### Trial design

This study is a single-center, randomized, controlled, quadruple-blinded, superiority trial, with two parallel arms and allocation 1:1, as recommended [16].

### Participants, interventions, and outcomes

#### Study settings and recruitment

The recruitment of the study participants will take place among both inpatients and outpatients of the Department of Paediatrics of the Medical University of Warsaw, Poland (academic hospital). The start of the recruitment is planned in September 2020 and should be completed over 24 months. For study recruitment in a similar single-center study with similar eligibility criteria [9], 28 months was a sufficient period.

#### Eligibility criteria

##### Inclusion criteria

At enrollment, the volunteer children must fulfill all of the following eligibility criteria to be considered for inclusion: (1) age at least 8 years and ≤ 18 years (regardless of race, ethnicity, gender); (2) FAP-NOS or IBS diagnosed according to the Rome IV Criteria [2]; (3) baseline average pain intensity at least 30 mm on a 100-mm Visual Analogue Scale (VAS) [9]; (4) feeding via the oral route; (5) ability to read and comprehend any employed questionnaires/scales; (6) signed informed consent; and (7) stated availability throughout the study period.

Participants with IBS and a stool consistency score > 5 on the Bristol Stool Scale will be classified as having IBS with predominant diarrhea (IBS-D); if the stool consistency score is < 3, the subjects will be classified as having IBS with predominant constipation (IBS-C) [16].

##### Exclusion criteria

The exclusion criteria are as follows: receiving any other intervention/treatment with regard to FAP-NOS or IBS or those who received any other intervention during the last 3 months, an organic cause of symptoms or organic gastrointestinal disease, chronic illness, receiving medications which affect gastrointestinal motility, need for any other dietary management which could make the balancing or compliance with the diet troublesome, previously diagnosed carbohydrate intolerance without symptoms of FAPD after implementation of an exclusion diet, undernutrition (defined as World Health Organization [WHO] [18] growth charts < − 2 SD [standard deviation]), decreased growth velocity (sharp decline in growth line), or overweight or obese (> 1 or > 2 SD on the WHO growth charts, respectively), unintentional weight loss greater or equal to 5% of subject’ body weight (BW) within the previous 3 months [16], pregnancy, eating disorders, prior surgery of the gastrointestinal tract (within last 3 months), recurrent or unexplained fever, and developmental disabilities which impair the ability of the child to understand or communicate.

#### Intervention

All eligible children will be assigned to one of two groups following the randomization sequence. For the design of the intervention, please see Fig. 1. For 4 weeks, children will receive a low-FODMAP diet or comparator – a regular diet. This period is recommended for clinical practice [3, 19], as it is a sufficient period for the majority of patients to achieve symptom improvement and for the investigators to observe adverse events associated with intervention.

**Fig. 1 Fig1:**
[figure not shown]
Flow chart of study design. Abbreviations: FAP-NOS, functional abdominal pain – not otherwise specified; FODMAPs, fermentable oligosaccharides, disaccharides, monosaccharides, and polyols; IBS, Irritable Bowel Syndrome; N, number of randomized participants; n, number of participants allocated to each group

##### Diets

The low-FODMAP diet will contain the amount of FODMAPs that will not exceed the cut-offs for each FODMAP sugar per serving of food per sitting, as adopted from Varney et al. [20]. The regular diet will reflect the habitual FODMAP intake in a normal diet (following Krogsgaard et al. [11]). No changes, except for the modification of FODMAP intake in the intervention group, will be imposed; diets in both groups will be matched in terms of total energy, fat, protein, carbohydrates and dietary fiber with the usual participant’s diet. The requirements of daily energy and nutrients will be calculated as mean values based on a quantitative analysis of a 3-day food record to reflect the each child’s habitual diet. The nutritional value of each meal plan in both groups will be calculated, using dietary software (DIETA 6.0; http://www.izz.waw.pl [2018, Warsaw, Poland]). All meal plans will be checked for FODMAP content with the Monash FODMAP Calculator (www.monashfodmapcalculator.com.au/), including: excess fructose, lactose, sorbitol, mannitol, fructans, galactooligosaccharides, and oligosaccharides.

Participants will receive five meals each day (3 main meals: breakfast, dinner, and supper; and 2 additional smaller meals: lunch and dessert). All meal plans will be individually tailored by a dietitian after the initial assessment. In case of additional hunger, additional low-FODMAP snacks will be supplied with the meal delivery each Monday (i.e., portion of nuts, granola bars, gluten-free biscuits, or crackers).

Diets will be delivered by a catering company each morning to each child’s residence as an all-day box-diet. The information on the recommended storage and, if needed, preparation of each meal will be included.

##### Study procedure and timeline

For the study procedure and timeline, see Table 1 and Fig. 1. At the initial baseline visit (Visit 0), children will be diagnosed with IBS or FAP-NOS by a gastroenterologist, undergo a growth assessment by a nurse, and have an initial visit with a research dietitian. At the initial dietary consultation, all subjects will receive oral and written information regarding the study. A Monash FODMAP-trained dietitian will educate the caregiver and child about the principles of the study design, as well risks and benefits, during a face-to-face meeting. The subjects will be asked to complete a questionnaire, reflecting the preceding week, including questions about the intensity and frequency of abdominal pain, stool consistency, absence from school, and parents’ absence from work. Baseline scores on the Gastrointestinal Symptom Rating Scale (GSRS) [21], the KIDSCREEN-10 index [22] and the World Health Organization Five Well-Being Index (WHO-5) [18] will also be obtained. The child’s anthropometric measurements will be obtained by an independent nurse (see Growth in Outcome section). The baseline dietary assessment will include a qualitative and quantitative assessment of each child’s usual food intake based on a 3-day food record completed retrospectively, against the Nutrition Standards for the Polish population (2017) [23]. Based on the same food record, the baseline FODMAP intake in each meal also will be calculated using the Monash FODMAP Calculator. The dietitian will perform a thorough interview to tailor the diet to the individual child’s needs [19, 24, 25]. The baseline physical activity level also will be assessed using a Moderate-to-Vigorous Physical Activity (MVPA) screening measure [26].

**Table 1 Tab1:**
[figure not shown]
Participant timeline

Whenever a patient is enrolled, the participant’s case report form (CRF) will be created. Both, the CRF and one copy of the informed consent in paper form will be archived. Data from the CRF will be entered into an electronic database (see Data collection and management section).

Participant will be randomized and allocated to receive the intervention or control diet for 28 days. During the intervention period, the abdominal pain intensity (using the 100-mm VAS score), stool consistency (using the Bristol Stool Form Scale), pain frequency (by reporting the number of episodes/week), school attendance and parents’ work absenteeism (by reporting the number of days of school or work/week missed), and scores on the GSRS, KIDSCREEN-10 index and WHO-5 will be recorded in the subject’s diary each week (see Table 1). For children ≥14 years of age, the study diary will be filled out by themself; for younger children, the diary will be filled out by caregiver. Moreover, the child/caregiver(s) will be reporting the percent of each meal which the subject consumed (< 50%, 50–79% or 80–100%) each day, to estimate the amount of food consumed throughout the trial; the additional snacks consumed also will be reported daily (characteristics and amount). The tolerance of the diet will be assessed each day using a 100-mm VAS and reported in the subject diary. The caregiver and/or participants will be instructed to record in the study diary any observations concerning the health of the child, especially any symptoms which appeared close to a meal. The dietitian will also monitor the subjects’ acceptability of and adherence to the provided diet each week (see Fig. 1).

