#### Outcomes

In agreement with recommendations [16], one primary outcome was pre-specified:
**Change in abdominal pain intensity.** Responders will be those with a daily reduction in the intensity of abdominal pain episodes of at least 30% at week 4 compared with baseline, and this value should be at least equal to the Reliable Change Index (RCI) for that sample [16, 27]. A cut-off of 25 mm for RCI change was adopted [16]. This outcome also will be assessed as the change at weeks 1, 2, and 3 from baseline.

For participant timeline, see Table 1.

Secondary outcomes to be assessed during the 4-week intervention, following the standardized core outcome set [17], will be:

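### For children under 14 the primary pain change may set the child's baseline rating against a caregiver's diary rating, and the responder rule asks for a daily reduction in a score recorded weekly

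*Protocol article*

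**What the plan says.** All places are in the protocol article.

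- **Baseline (Study procedure and timeline, Visit 0):** "The subjects will be asked to complete a questionnaire, reflecting the preceding week, including questions about the intensity and frequency of abdominal pain".
- **Follow-up (same section, after Table 1):** pain VAS, with the other symptom and quality-of-life scores, "will be recorded in the subject’s diary each week". On who completes it: "For children ≥14 years of age, the study diary will be filled out by themself", and "for younger children, the diary will be filled out by caregiver".
- **What is scored daily on a VAS (same section):** "The tolerance of the diet will be assessed each day using a 100-mm VAS". Pain is not described as a daily entry.
- **Responder rule (Outcomes):** "Responders will be those with a daily reduction in the intensity of abdominal pain episodes of at least 30% at week 4" against baseline, with the change also at least the Reliable Change Index, set at 25 mm. The abstract gives the same two thresholds, but for improvement over the final week, without the word daily.
- **Eligibility (Inclusion criteria):** every child is aged 8 or over and must have "ability to read and comprehend any employed questionnaires/scales".

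**The concern.** A change score is interpretable when the same person uses the same scale at both ends. Here the baseline is attributed to the subjects and the follow-up diary, below age 14, to the caregiver. If caregivers judge the pain themselves, any systematic child-caregiver difference is added to the change, and any random disagreement adds noise to it. The primary outcome then cuts that change at a fixed 25 mm, so children can cross the line because the rater changed rather than the pain.

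The responder rule has its own problem. As worded in Outcomes, it refers to a daily quantity that the described data collection does not produce. Two analysts could build the primary endpoint differently: one from the single week-4 score, another looking for day-by-day pain data.

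Neither matter can be settled properly in the analysis. A statistical analysis plan cannot recover a rating that the child never gave or a score that was never collected daily.

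**Working it through.** **1. Who rates.** Set side by side, the two passages in Study procedure and timeline name different people for children under 14: the subjects at Visit 0, the caregiver from week 1. The same section elsewhere separates the child or caregiver who reports meals from the subject who ate them, which supports reading subjects as the children. This is the plain reading, though not the only possible one (see objection).

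**2. How many children.** No age distribution is given. Ages 8 to 13 are 6 of the 11 completed-year bands from 8 to 18. If ages were uniform (assumption), 6/11 = 55% would have a caregiver-completed diary.

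**3. Which threshold decides.** The 30% rule equals 25 mm at a baseline of 25/0.30 = 83.3 mm. Below that baseline the 25-mm limit is the stricter one and decides response. A 10-mm rater offset is 10/25 = 40% of that limit.

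**4. Effect of a constant offset.** The documents give no means, SDs or child-caregiver differences, so these are assumptions: mean fall 15 mm on the regular diet and 30 mm on the low-FODMAP diet, SD of the fall 20 mm, response if the fall is at least 25 mm. With a normal approximation, P(response) = 1 − Φ((25 − mean fall)/20).

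| Rating at week 4 | Regular diet | Low-FODMAP | Contrast |
|---|---|---|---|
| Same rater (falls 15, 30) | 1 − Φ(0.50) = 30.9% | 1 − Φ(−0.25) = 59.9% | 29.0 points |
| Caregiver scores 10 mm lower (25, 40) | 1 − Φ(0) = 50.0% | 1 − Φ(−0.75) = 77.3% | 27.3 points |
| Caregiver scores 10 mm higher (5, 20) | 1 − Φ(1.00) = 15.9% | 1 − Φ(0.25) = 40.1% | 24.3 points |

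The response level moves by 15 to 20 points in each arm, but in the same direction, so the contrast loses only 1.7 to 4.7 points among caregiver-rated children. With 55% caregiver-rated, the whole-trial contrast is 0.45 × 29.0 + 0.55 × 27.3 = 28.1, or 0.45 × 29.0 + 0.55 × 24.3 = 26.4 points.

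**5. Adding random disagreement.** A simulation of the full rule (30% and 25 mm) used the same falls, a baseline of mean 55 mm and SD 18 restricted to 30 to 100 mm, and week-4 scores kept within 0 to 100 whenever they were computed. Same-rater response was 30.6% vs 59.8%, a contrast of 29.2 points. With 40 to 80% caregiver-rated, offsets of −10, 0 or +10 mm and added rater SD of 10 or 20 mm, regular-diet response ranged from 21% to 46% and the contrast from 21 to 28 points. Noise matters without any offset: at 60% caregiver-rated and zero offset, the contrast was 27.3 points with SD 10 and 24.0 with SD 20.

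**6. The plan's sample size.** It gives 31 per arm for a 30% difference but states no control rate, so the figure cannot be checked against this model. The point does not depend on it.

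**7. Daily or weekly.** Three statements have to agree: a daily reduction (Outcomes), a weekly diary entry (Study procedure and timeline) and improvement over the last week (abstract). The second and third fit together; the first fits neither.

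**The case against.** The strongest reply is that the rater switch is inferred. The protocol also calls the diary the subject's when a caregiver completes it, so the word subject does not reliably identify the rater. The baseline questionnaire asks about parents' absence from work, which a caregiver would naturally answer. Filling out a diary says who writes, not who judges, and a child who must understand the scales could well give the rating for a caregiver to record. This stands in part: if the caregiver only transcribes, or also supplied the baseline, the switch disappears. But the text says neither, and staff following it literally would produce the switch.

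Several stronger readings are tempting and are not supported:

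- *Baseline is recall and follow-up is not.* Both appear to cover about a week, so the rater is the only contrast.
- *The primary outcome cannot be computed.* The abstract's rule can be computed from weekly scores; the fault is one conflicting word. Table 1 is not shown, but the text cites it alongside the weekly recording.
- *The quality-of-life and symptom scales certainly share the defect.* For GSRS, KIDSCREEN-10 and WHO-5 the baseline scores are only said to be obtained, with no rater named. The risk is plausible but less explicit.
- *The trial is biased towards one diet.* The age rule is the same in both arms, and children and caregivers are to be blinded. If blinding holds, the error is non-differential.
- *The 15 to 20 point movement is the damage to the comparison.* That is a shift in level in both arms; the contrast changes far less.

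It is also fair that an age-based diary rule is not in itself an error. The fault is that the plan does not hold the rater constant within the child.

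**Conclusion.** The point holds as a conflict in the stated text that should be corrected. For children under 14 the primary change may compare self-report with caregiver report, and the responder definition in Outcomes disagrees with both the recording schedule and the abstract. The consequence is avoidable misclassification at a cut that is 25 mm for every baseline below 83.3 mm, with modest loss of contrast: from about 29 to 24 to 27 points among caregiver-rated children for a constant 10-mm offset, and to 21 to 28 points over the whole trial in the scenarios with added noise. The mean falls, SDs, baseline distribution, rater offset, rater noise and caregiver-rated share are all assumed, so the figures show direction and order of size only. The documents do not establish that caregivers will judge the pain, nor that either arm would be favoured.

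**What to change.** 1. State that the same person rates the pain VAS at baseline and at weeks 1 to 4 for each child. The child is the better choice, given the eligibility requirement on understanding the scales, with the caregiver only assisting or transcribing.
2. Apply the same rule to GSRS, KIDSCREEN-10 and WHO-5, and name their baseline rater.
3. Delete the word daily from the responder definition in Outcomes, so that response is the week-4 weekly VAS against the baseline weekly VAS, with a fall of at least 30% and at least 25 mm. This matches the abstract and the diary schedule.

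The cost is new diary instructions, a wording change in Outcomes, ethics approval of the amendment, and slightly more effort for the youngest children. Recruitment was planned from September 2020, so some children may already be enrolled. For them, changing the reporter midway would itself mix raters: keep whoever rated the baseline wherever that is still possible, and record who gave each rating. Collecting pain VAS daily and averaging over seven days at both ends would also resolve the daily wording, but it adds a daily baseline week and more burden, and it is not needed for the abstract's rule.

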##### Concomitant care

Before enrollment, screening and baseline assessment of each subject is planned, as recommended [16]. All necessary laboratory, imaging, and endoscopic tests will be performed to rule out diseases that may mimic FAPD symptoms (e.g., celiac disease). Any psychological comorbidities also will be determined. In case of use of concurrent medication(s), the mechanism of drug action and potential influence on the intervention effect will be evaluated by a physician. However, enrolled subjects will be encouraged to maintain their usual dose and administration schedule of concomitant medications during the entire study period. No physical activity advice will be provided, as it is not the part of this intervention. During the study period, the caregiver(s) will be discouraged from starting any new dietary, pharmaceutical, or any other complementary or alternative treatments which could affect FAPD symptoms (e.g., selective serotonin reuptake inhibitors, unusual exercise, or probiotics). In case of any new treatment imposed, the participant or caregiver will be instructed to report this in the study diary. In case of the need for any rescue medication for FAPD, this will be prescribed by the investigator and noted in the CRF. Each commencement of new aforementioned therapy will be treated as a protocol violation and such patients will not be included in the per-protocol analysis.

##### Criteria for discontinuing the intervention

Withdrawal of informed consent is possible at any time, without any obligation for the child or caregiver to give reasons for the decision. Diet tolerance, compliance, and adverse events will be monitored during each control visit or call (see Fig. 1). Twenty-four phone contact to the study site will be available for all participants. An independent Data and Safety Monitoring Board (DSMB) will be appointed prior to study commencement to evaluate each reported adverse event (see Monitoring section). In case of occurrence of any serious adverse events or new circumstances affecting the safety of the child, the intervention will be discontinued. The reason and timing of any withdrawal (i.e., non-compliance, withdrawn consent, adverse events) will be documented.

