##### Compliance

A controlled feeding trial, as is considered to be the gold standard for evaluating dietary interventions, may enhance the subjects’ adherence to the intervention and decrease confounding dietary habits. At the initial visit, each subsequent visit and during each call with the dietitian, participants will be encouraged to maintain adherence to the study protocol. Any individual issues associated with the diet will also be discussed. Compliance with the study protocol will be evaluated by aforementioned direct interview with child and/or caregiver and analysis of data from the subject diary. The percentage compliance in each group will be calculated by the dietitian. In agreement with other studies, a compliant participant is considered as one who consumes at least 80% of the provided diet [9, 15]. Snacks and meals outside the meal plan will be assessed separately.

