**Change in stool consistency.** Responders will be subjects with improvement in their average stool consistency during the last week of the trial compared with baseline [≥1 higher Bristol Stool Scale score in case of IBS-C, or at least one lower score in case of IBS-D] [16]. The change at weeks 1, 2, and 3 from baseline also will be measured.**Change in abdominal pain frequency** at weeks 1, 2, 3, and 4 from baseline [16].**Change in GSRS** [21] **total score** at weeks 1, 2, 3, and 4 from baseline.**Change in KIDSCREEN-10 index** [22] **total score** at weeks 1, 2, 3, and 4 from baseline.**Change in WHO-5** [18] **total score** at weeks 1, 2, 3, and 4 from baseline.**Change in percentage of school attendance** associated with IBS symptoms (at weeks 1, 2, 3, and 4 from baseline).**Change in percentage of parents’ work absenteeism** associated with IBS symptoms in child (at weeks 1, 2, 3, and 4 from baseline).**Change in BMI-for-age z-score**. The BW (kg) and standing height (cm) will be measured following standard methods by an independent nurse at baseline, after 2 weeks, and after 4 weeks. Body Mass Index (BMI) will be calculated using the standard eq. BMI-for-age z-score will be computed using the WHO AnthroPlus software v1.0.4., then assessed and monitored over time using the WHO growth charts by a dietitian.**Percentage of compliant participants** (see Compliance section).**Percentage of tolerability of the low-FODMAP diet.** This outcome will be reported as a mean for each study group, and as a comparison between groups (MD [mean difference] with 95% CI).**Adverse events.** The number of all adverse events and the number of participants reporting adverse events associated with the intervention (with characteristics) will be reported for each study group (see Criteria for discontinuing the intervention and Harms sections).

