#### Blinding

This is a quadruple-blinded trial. In addition to the subjects, the research investigators (AH, HS), outcome assessor (AH), and independent statistician (data analyst) will be blinded until the completion of the data analysis. The participants and their caregivers will be not informed about the characteristics of the diet being consumed (the name and description will not be provided, as in similar previous RCTs [28, 29]). The researcher will encourage the caregivers/participants not to attempt to identify the nature of the provided diet using available data sources; however, an associated bias cannot be excluded. Therefore, after completion of the follow-up period, each participant and outcome assessor will be asked whether he/she believes that active treatment was administered (these data will be published with the final results, as recommended) [15]. The dietitian (AS) will remain unblinded. The procedure was established to maintain separation between the dietitian and outcome assessor and analysts. The primary outcome will be assessed by a blinded researcher (AH). If possible, to increase the similarity of diets in the two groups, low-FODMAP substitutes will be provided in place of high-FODMAP products in the meal plans.

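### Adverse events are gathered partly through calls with the unblinded dietitian, and the only per-child safety count is restricted to events judged related to the diet, so knowledge of the allocation may influence it

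*Protocol article*

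**What the plan says.** Four places in the protocol article bear on this.

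- **Collection.** Criteria for discontinuing the intervention: "Diet tolerance, compliance, and adverse events will be monitored during each control visit or call (see Fig. 1"). No person is named.
- **Who makes the calls.** Compliance: "At the initial visit, each subsequent visit and during each call with the dietitian, participants will be encouraged to maintain adherence to the study protocol". The study procedure section adds a weekly contact: "The dietitian will also monitor the subjects’ acceptability of and adherence to the provided diet each week (see Fig. 1"). That sentence does not mention adverse events.
- **Blinding.** The Blinding section says of the dietitian that this person "will remain unblinded. The procedure was established to maintain separation between the dietitian and outcome assessor and analysts". The investigators, the outcome assessor and the statistician are listed as blinded. A blinded researcher is assigned specifically to the primary outcome; nobody is named for adverse events.
- **Definition of the outcome.** Outcomes lists two measures per arm. One is the total number of adverse events. The other is a count of children: "the number of participants reporting adverse events associated with the intervention (with characteristics) will be reported for each study group". The Harms section has every event entered in the case report form (CRF) and evaluated for its causal relationship with the diet, without saying who evaluates it or whether that person is blinded.

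**The concern.** Two features act together. First, an interviewer who knows that a child is on the restricted diet may ask about symptoms more closely, or less closely if hopeful for the diet, and so change how many events are recorded. Second, the only measure that counts children, and hence the only listed one that gives a percentage, a relative risk or a number needed to treat for adverse events, passes through a causality judgement. Events on a regular diet are easily judged unrelated. A rater who knows or guesses the arm could therefore create or hide a difference.

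The total number of events has no causality filter, but it cannot replace the missing count. One child may contribute many events, so the total does not say how many children were affected. The trial is presented as quadruple-blinded and is meant to inform guidelines, so the safety comparison deserves a definition that does not rest on attribution.

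**Working it through.** The plan gives no adverse-event rate and no safety calculation, so there is no figure to reproduce. The check is a side-by-side reading followed by an illustration.

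**Reading**

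1. Events are monitored at visits or calls. The calls described are with the dietitian, and the dietitian is unblinded. So at least part of the elicitation runs through someone who knows the allocation.
2. For visits the link is not established. Visit 0 involves a gastroenterologist, a nurse and a dietitian, and an independent nurse measures the children at baseline and after 2 and 4 weeks. Fig. 1 and Table 1, which might settle the point, are not available.
3. Causality is evaluated, but no rater is named. The filter on the per-child count is therefore certain; who applies it is not.

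**Illustration**

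Inputs: 37 children per arm (Sample size section). Assumed: the same true proportion *p* of children with at least one event in both arms (20%, 40% or 60%), and a probability of being counted as related of *a1* in the diet arm and *a0* in the control arm.

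Reported proportions: q1 = p × a1 and q0 = p × a0. Relative risk (RR) = q1/q0 = a1/a0, whatever *p* is:

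- 50% against 50%: 0.5/0.5 = 1.0
- 60% against 40%: 0.6/0.4 = 1.5
- 70% against 30%: 0.7/0.3 = 2.33

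Chance that this false difference reaches two-sided p < 0.05, by normal approximation: Φ[(|q1 − q0| − 1.96 × se0)/se1], with se0 = √[2q̄(1 − q̄)/37], q̄ the mean of q1 and q0, and se1 = √{[q1(1 − q1) + q0(1 − q0)]/37}.

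Worked case, p = 40%, 70% against 30%: q1 = 0.28, q0 = 0.12, q̄ = 0.20; se0 = √(0.32/37) = 0.0930; se1 = √[(0.2016 + 0.1056)/37] = 0.0911; (0.16 − 0.1823)/0.0911 = −0.24; Φ = 0.40.

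The last column gives the same chance for the Fisher exact test, summed over all pairs of binomial counts with 37 per arm. The plan allows that test, and the expected counts are small.

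| p | Attribution | Expected children counted (37 × q) | RR | Normal approximation | Fisher |
|---|---|---|---|---|---|
| 20% | 60% / 40% | 4.4 / 3.0 | 1.5 | 8% | 3% |
| 40% | 60% / 40% | 8.9 / 5.9 | 1.5 | 14% | 9% |
| 60% | 60% / 40% | 13.3 / 8.9 | 1.5 | 20% | 14% |
| 20% | 70% / 30% | 5.2 / 2.2 | 2.33 | 21% | 10% |
| 40% | 70% / 30% | 10.4 / 4.4 | 2.33 | 40% | 31% |
| 60% | 70% / 30% | 15.5 / 6.7 | 2.33 | 62% | 54% |

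A count of children with an event of any cause stays at RR 1.0 in every row, because attribution does not enter it. It remains open to differential elicitation, so the fix needs both parts.

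**The case against.** The strongest reply is that the plan already has several safeguards. The total number of events is reported per arm, and every event goes into the CRF, so unattributed events are not lost. Health observations, and a daily tolerance score, are written in the diary by children or caregivers who are not told which diet they receive. An independent safety board evaluates each reported event. A blinded outcome assessor is listed in general terms. Children with any event can be tabulated from the CRF, and naming the causality rater is detail that an article may leave to the full protocol.

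Much of this stands, and it rules out stronger readings that a reader might infer.

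- **That the dietitian runs the visits, rates causality, or is the safety assessor.** No section says so. The separation claimed in the Blinding section is therefore not shown to be broken for adverse events.
- **That the dietitian's part in growth and compliance proves the point.** For growth, the z-score is "then assessed and monitored over time using the WHO growth charts by a dietitian", but an independent nurse takes the measurements and software computes the score. The compliance percentage is calculated by the dietitian, but partly from diary entries. Neither is elicitation or attribution of adverse events.
- **That the whole safety comparison depends on knowledge of the allocation.** The total count carries no causality filter.

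What the reply does not remove: diaries do not prevent uneven probing during calls; the board can only evaluate events that were reported, and its own blinding is not stated; and the outcome definition itself chooses the filtered count as the only per-child measure. That last point is a stated rule, not missing detail.

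**Conclusion.** The point holds in a narrow form. Adverse events are gathered partly at calls with a person who knows the allocation, so recording may be influenced by it. The only per-child adverse-event outcome depends on a causality judgement with no stated blinded rater.

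The size is not known. If attribution differs between arms while true risk is equal, the apparent relative risk is 1.5 for 60% against 40% and 2.33 for 70% against 30%. Over assumed any-event rates of 20% to 60%, the chance of a nominally significant false difference is about 8% to 20% in the milder case and 21% to 62% in the stronger one by normal approximation. With the Fisher test it is lower: 3% to 14% and 10% to 54%. These results rest wholly on assumed rates and on a rater who knows or guesses the arm, which the documents do not establish. This is a minor point, worth correcting because the correction is almost free. The primary outcome is not touched.

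**What to change.** In Outcomes, make the between-arm safety comparison the number of children per arm with at least one adverse event of any cause, taken from the CRF and diary. Keep the total number of events, and show children with related events as a second measure.

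In Harms and Blinding, state that events are elicited with one standard question by a team member whom the protocol already blinds, and that causality is rated by such a person. An investigator meets this condition; the nurse is described as independent, so would qualify only if confirmed blinded. The dietitian passes on any event heard during a call without rating it.

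The cost is a few sentences of protocol wording and a small shift of tasks among existing staff. The any-cause count needs no new data, because all events are already to be entered in the CRF.
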